#### **6.4.6 Equipment provision**

All care homes will be provided with at least one tablet to aid live data collection. In addition, care homes allocated to the intervention will be provided with the following equipment:

- Up to 21 air filters whereby a maximum of 16 will be placed in private bedrooms and 5 in communal areas (location to be decided during site set up). The final number of air filters will depend on the number of “consented” residents within each care home, which will in turn partly depend on the size of the care home.
- Energy meters (same number as air filters)
- Extension cords (as required)

### **6.5 Individual resident invitation**

#### **6.5.1 Identification of individual residents**

The anonymised study register (see section 6.4.3) will be sent to the study team to create a random order of eligible residents for the care home managers/study champions to approach and invite residents to receive an air filter in their private bedrooms and/or provide access to their medical records and share identifiers with the

UKHSA. If the staff recruiting approach the first residents randomly selected for consent on the list and some decline, the study team will request they work their way down the random list until they have consented enough residents. The average number of residents consented at each care home will be 12. Some larger care homes will be asked to recruit more residents to make up for fewer residents being consented at smaller care homes. The maximum number of residents that will be consented at any care home will be 16.

Residents will have the option to opt out of any data being collected about them (see section 6.15.3). This will be recorded on the register.

### **6.5.2 Invitation**

Trained staff (managers and study champions) will be asked to provide the relevant invitation materials to the randomly selected eligible residents. Resident Information Sheets (RIS; provided in written, audio, picture and video formats) will be provided to residents/consultees to enable them to decide whether or not they would like to be one of the “consented” residents at that site. A letter will be sent to the GP of residents who consent to take part in the study.

If a resident is selected that does not have capacity, a suitable Consultee will be identified. This will either be a Personal Consultee (relative or close friend), or a Nominated Consultee (someone who is not a member of the care home staff and who is independent of the study). If a suitable Consultee cannot be identified, the resident will not be approached to be one of the “consented”. See section 7 for further information.

### **6.6 Consented residents baseline data collection**

For eligible and consented residents, the following baseline data will be collected on an individual level: name; date of birth; sex; ethnicity; NHS number; receiving nursing care, infection symptoms.

Study champions will ask eligible and consented residents to complete the resident infection prevention and control & care home satisfaction questionnaires (see section 6.11).

Consented residents in the intervention arm will receive an air filter for the winter period. For further information regarding consent procedures, see section 7.

### **6.7 Resident data collection during winter period**

Data will be collected on up to approx 30 eligible residents (“the 30”) in the winter months (usually defined as 1 September to 31 May- assuming COVID-19 is still prevalent). The pool of “the 30” residents will be randomly selected from all eligible residents on the resident register. The random selection will be carried out either via the study database or, if required for technical reasons, by the study statistician. If a resident in the pool of “the 30” opts out of the study, another randomly selected eligible resident will be selected to replace them. Where the care home has  $\leq 30$  eligible residents, data will be collected for all eligible residents. During the winter period, the air filters will be switched on in the intervention care homes (following 2 days of data collection at baseline). Data may be collected on a paper CRF, on a daily basis and entered into the database at the end of each week or entered directly into the database on a daily basis.

Data collection will begin once sufficient residents have been approached and consented in both control and intervention care homes. Usually “sufficient” residents would be considered to be at least 7. Every effort will be made to consent residents as soon as possible in each care home for both groups. Data collection should start no earlier than the 1 September.

For the intervention care homes, data collection should start no earlier than the 1 September. Two days of data collection is required before the air filter units are switched on.

The resident register (section 6.4.3) will be kept up to date throughout the care home data collection period with resident eligibility and basic information. Resident absences from the care home will be recorded. Residents joining the care home will be added to the register up until 1 May.

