### **10.3 Distribution of air filters**

Air filters will be shipped by Phillips to a logistic company in the UK. Once the care home has completed site set-up and been randomised to the intervention arm, the central study team will liaise with logistics company to notify them how many air filters are required to be delivered to the care home. Delivery will be directly from the logistics company to the individual care homes.

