### **10.4 Installation and use of air filter units**

On delivery care homes will confirm receipt of the air filter units, unpack them and confirm that there has been no damage. Units will be labelled with a unique ID. The units are 'plug in and go' and care homes will be supported by the study team with installation and location of the air filters. The study team will ensure room location and set up is as per manufacturer advice. This process is straightforward, the device is removed from transport packaging and plugged into an energy meter, which plugs into the wall. Energy monitors will record unit operating time. Care homes will be asked to check they can plug in the air filters / energy meters to electrical sockets on receipt, without switching on the filters. Extension leads can be provided if needed.

When data collection starts, care homes will be required to enter 2 days of data collection before the air filters can be switched on. Once the care home have installed both communal and private bedroom the 'plug in and go' air filters, they will be advised to keep the air filter switched on at all times. The advice is to keep the air filters on 1 fixed mode consistently. They may want to adjust to the different modes to decide which one(s) are preferable to them, down to personal preference and whether there are different modes preferred between day and night time.

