Based on 90% power and an alpha of 0.05, to detect a reduction in winter respiratory infections of 1 per 242 person days from 2 to 1 per 242 person days, assuming a coefficient of variation of 0.78 to allow for between care home infection rate variation, calculated from data provided in personal communication from the PRINCESS study team,(34) a total of 74 care homes will be required. This assumes a mean cluster size of 12 for winter 3 (10 participants per care home for winters 1 & 2) and accounting for an attrition level as observed in PRINCESS,(34) and the continual recruitment strategy as described above, each cluster will provide a mean of 1920 person days of follow up. After reviewing accumulating data with the DMC and TSC on the number of follow up days, a decision was made to increase the number of care homes taking part in Winter 3 from 32 to 46 in order to achieve the number of person days required in the original calculation. This gives an approximate total of 91 care homes taking part in the study overall.

Each care home will participate for a single winter season (usually 1 Sept to 31 May). We estimate that 10 care homes will be randomised in winter 1 (the most experienced) and then 35 in winter 2 and 46 in Winter 3.

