#### 13.1.2 Data and statistical analysis

Analyses and reporting will be according to CONSORT guidelines(49) and will be pre-specified prior to the analysis in a detailed statistical analysis plan. Baseline data will be presented by trial arm, for both individual- and cluster-level characteristics, using descriptive statistics. Continuous measures will be presented using a measure of central tendency and variation as appropriate and categorical data as frequencies and percentages.

The primary effectiveness analysis will be conducted on the "consented" under the intention to treat principle (ITT) using mixed effects Poisson regression to estimate an incidence rate ratio (along with associated 95% confidence interval and p-value), comparing incidence of resident winter respiratory infection between groups. The primary analysis model will adjust for nursing care provision and deprivation tertile (stratification variables) and will include a random effect for care home to account for clustering. The use of a mixture distribution that captures the variation in rates across care-homes, and/or zero inflated models will be explored dependent on the nature of the data obtained. Robust standard errors will account for clustering if mixed effects models fail to converge.

The effect of the intervention on secondary outcomes in the "consented" will be investigated using the same analytical approach as in the primary analysis; using mixed effects regression models that are appropriate to the nature of the outcome being analysed (e.g. a logistic model for a binary outcome). Analyses will be repeated using anonymous data collected on all residents.

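### Start of follow-up is triggered by consent after unblinded allocation, and the stated primary model has no calendar term, so season can bias the rate ratio if start dates differ by arm

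*Protocol*

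**What the plan says.** - **Order of events.** Section 6.4.5 places randomisation first. Homes then learn their allocation, intervention homes complete additional device training, and only then do their staff start inviting residents. For control homes the section lists invitations but no extra training. Section 7.2 makes the information sheets specific to the allocation.
- **Start of follow-up.** Section 6.7: "Data collection will begin once sufficient residents have been approached and consented in both control and intervention care homes". The usual threshold is at least seven consented residents. The earliest date is 1 September and no latest date is given. The same section promises prompt consenting in both groups.
- **End of follow-up.** Section 2.4 usually ends winter on 31 May, for every home.
- **Filters.** Section 10.3: "Once the care home has completed site set-up and been randomised to the intervention arm, the central study team will liaise with logistics company". Section 10.4: "care homes will be required to enter 2 days of data collection before the air filters can be switched on".
- **Primary analysis.** Section 13.1.2 specifies a mixed effects Poisson model, "comparing incidence of resident winter respiratory infection between groups", adjusted for nursing care provision and deprivation tertile, with a random effect for home. Mixture or zero-inflated versions may be explored. No term for calendar time, start date or winter is named.
- **Related safeguard.** Section 6.17 plans sensitivity analyses of continual recruitment, including a check for recruitment bias after randomisation. It does not mention calendar time.

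**The concern.** A home's start date is settled after its allocation is known, by how quickly residents agree to an arm-specific request. The end date is essentially common, so a later start removes the early part of the season and leaves the rest.

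Respiratory infection varies over the winter. A home that starts after the peak has a lower crude rate for that reason alone. If such starts are commoner in one arm, the rate ratio picks up season as well as filters. The home random effect does not correct this, because it is assumed independent of arm. Winter is neither a stratification factor nor a named covariate.

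At stake is an avoidable objection to an open-label comparison of a seasonal outcome, whether the imbalance arises systematically or by chance.

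**Working it through.** **1. The plan's own figure.** Section 13.1.1 gives "Based on 90% power and an alpha of 0.05", rates "from 2 to 1 per 242 person days", "assuming a coefficient of variation of 0.78" and "each cluster will provide a mean of 1920 person days of follow up". I took alpha as two-sided. The Hayes-Bennett formula for unmatched clusters is

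c = 1 + (z₁ + z₂)² × [(λ₀ + λ₁)/y + k²(λ₀² + λ₁²)] / (λ₀ − λ₁)²

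with λ₀ = 2/242, λ₁ = 1/242, k = 0.78, y = 1920 and (1.960 + 1.282)² = 10.507:

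- (λ₀ + λ₁)/y = 6.46 × 10⁻⁶
- k²(λ₀² + λ₁²) = 5.194 × 10⁻⁵
- (λ₀ − λ₁)² = 1.708 × 10⁻⁵
- c = 36.94, so 37 per arm and 74 homes.

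The stated 74 is reproduced. The calculation uses one rate per arm with no time dimension, and this point does not alter it.

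**2. Effect of a one-month slip on one home.** The protocol gives no seasonal curve, so two are assumed (relative rates, September to May):

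- A (peak to trough 2.5:1): 0.8, 1, 1.2, 1.5, 1.4, 1.1, 0.9, 0.7, 0.6
- B (6:1): 0.6, 0.8, 1.2, 2.4, 1.6, 0.9, 0.8, 0.6, 0.4

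The home's crude rate is the mean from its start month to May.

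| Start month | A: mean | A: change on slipping one month | B: mean | B: change on slipping one month |
|---|---|---|---|---|
| Sep | 1.022 | +2.7% | 1.033 | +5.2% |
| Oct | 1.050 | +0.7% | 1.088 | +3.8% |
| Nov | 1.057 | −2.3% | 1.129 | −1.1% |
| Dec | 1.033 | −9.0% | 1.117 | −23.0% |
| Jan | 0.940 | – | 0.860 | – |

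**3. Effect on an arm.** If a quarter of intervention homes slip from December to January and no control home does, the arm rate falls by 0.25 × 9% to 0.25 × 23%, about 2% to 6%, with no true effect.

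**4. Cross-check with a different curve.** Assume a log-sinusoidal season, peak to trough 2 to 5, peaking on 1 December or 1 January. The null rate ratio is the mean rate over the intervention window divided by the mean over the control window, both ending 31 May. For rejection rates, restoring 74 × 1920 = 142,080 person-days over 91 homes gives about 1561 per home, or 1561 × 2/242 = 12.9 events. Then SE(log rate ratio) = √[2 × (1/12.9 + 0.78²)/45.5] ≈ 0.174.

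| Control start | Intervention lag, whole arm | Null rate ratio | Type I error |
|---|---|---|---|
| 1 October | 28 days | 0.97 to 1.02 | 0.05 to 0.055 |
| 1 December | 14 days | 0.93 to 0.98 | 0.05 to 0.07 |
| 1 December | 28 days | 0.85 to 0.96 | 0.06 to 0.16 |
| either | none | 1.00 | 0.05 |

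**5. Which starts does the protocol plan?** Table 3 and its footnote put baseline in August and follow-up from 1 September for winters 2 and 3, which is 35 + 46 = 81 of 91 homes. Section 3.2 gives the winter 1 pilot up to six months ending 31 May, so about 10 homes (10/91 = 11%) would start around December or later. If every winter 1 intervention home, and no control home, slipped a month from December, the arm rate would move by 0.11 × 9% to 0.11 × 23%, about 1% to 2.5%.

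**The case against.** The strongest reply is that no difference by arm is documented. Section 6.7 applies the same trigger to both arms and commits to prompt consenting in both. If start dates have the same distribution, seasonality does not bias the ratio systematically. That stands, and it rules out several readings that a reader might draw:

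- **That season does confound the result.** The text shows that it can, not that it does.
- **That the Poisson model wrongly takes the rate as constant.** The protocol does not say so. A count over person-time estimates an average rate, and this is harmless when the arms' windows match.
- **That delivery and installation hold back the intervention arm's data.** Sections 10.3 and 10.4 do not make data collection wait for units. Section 10.4 requires data before switch-on.
- **That consent to a bedroom device is needed to reach the threshold.** Sections 2.5 and 5.2.1 allow consent to a filter, to notes review, or to both. The filter offer could even speed consent.
- **That any bias must favour the filters.** For early-autumn starts the sign can go either way.
- **That the shortfall in person-days shows late starts in one arm.** About 1561 against 1920 per home (19% lower) fits shorter follow-up overall but says nothing about arms.

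It is also fair that the trial is powered for a rate ratio of 0.5. A 6% shift is about 0.062/0.174 = 0.36 standard errors, which takes type I error from 0.05 to about 0.065. Finally, the analysis plan is not at hand and may already split person-time. What remains is that the protocol names its primary covariates, defines the window by an event after allocation that may depend on arm, and names no safeguard for calendar time.

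**Conclusion.** The point holds as a conditional risk. Start dates follow unblinded allocation, have no latest limit and may differ by arm in either direction. The stated model would not adjust for the resulting difference in season.

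Under the assumed curves the distortion is about 5% or less per month of slip in an affected home for September to November starts, the range planned for most homes. It is about 9% to 23% for a slip from December to January. Effects at arm level are smaller in proportion to the share of homes affected, and the systematic bias is zero if start dates are balanced. These sizes rest on assumed seasonality and lags, because the protocol supplies neither. The change is worth making because it is cheap and also removes chance imbalance in calendar time. The sample size is not in question.

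**What to change.** - Split each resident's days at risk and episodes by calendar period, with log days at risk in the period as the offset, and add period to the primary Poisson model. Month within winter is the natural choice. If convergence is a problem, use a coarser period, or a smooth seasonal term plus winter.
- At minimum, pre-specify this as a sensitivity analysis of the primary result.
- Tabulate start date and the interval from randomisation to start, by arm and winter.

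The cost is a paragraph of analysis wording and a data-restructuring step; daily symptom records are already collected. Month-within-winter terms add roughly 20 to 25 parameters. Since section 13.1.2 already anticipates possible non-convergence, the coarser fallback should be named in advance.

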### 6.7.1 Data collected on up to 30 ELIGIBLE residents in intervention and control arms

The following data will be collected on up to 30 eligible residents in an anonymised format (unless they opt out of the study);

- **Infection symptoms** (Frequency: Daily): Any new (or worsening of pre-existing) respiratory symptoms including: runny/blocked nose; sneezing; sore/tickly throat; earache; runny ear; red/sticky eye/s (part of the respiratory tract due to the lacrimal duct); hoarse voice; cough; wheeze; noisy breathing; sputum (phlegm); chest pain; and/or shortness of breath, loss and/or change in taste/smell, vomiting, diarrhoea, delirium and/or confusion, deterioration in physical ability, fever (highest temperature).
- **Antibiotic consumption** (Frequency: Daily): Study champions use whichever data source is most appropriate, including direct discussion with the resident and/or consulting care home drug charts. For residents with capacity, where the drug chart and resident disagree, the resident's view will take priority.
- **Frequency of adverse events** (Frequency: Daily): Any falls or near falls using PROFANE (Prevention of Falls Network Europe consensus, see <http://www.profane.eu.org/>) definitions respectively for falls as "an unexpected event in which the participants come to rest on the ground, floor, or lower level".

### 6.7.2 Data collection on ALL CONSENTED residents in intervention and control arms

- **Infection prevention control strategies questionnaire** (frequency: end of March): see section 6.12.
- **Care home satisfaction questionnaire** (frequency: end of March): see section 6.12.
- **Additional care** (frequency: daily): The resident register for consented residents will include details of additional care received outside of the care home (e.g. primary care contacts).
- **End of follow-up medical notes review.** The central study team will contact the relevant GP practice for those residents and ask them to provide data between baseline and end of follow-up. Data will include: medically diagnosed infections (respiratory, urinary, gastrointestinal and skin/soft tissue infections); number and names of antibiotic prescriptions, hospital admissions\*, adverse events and GP consultations.

### 6.7.3 Data collected on CONSENTED residents in INTERVENTION arm only

- **Air filter Satisfaction questionnaire** (frequency: end of March): see section 6.12.

## 6.8 Care home follow up data collection

Care home level follow up data will commence as defined in section 6.7.

### 6.8.1 Care home follow up data collection in ALL care homes

- **Infection prevention control strategies questionnaire** (frequency: end of March): see section 6.10.
- **Care home satisfaction questionnaire** (frequency: end of March): see section 6.10.
- **Staff absenteeism** (frequency: daily/weekly) – managers will anonymously report absenteeism, number of days absent and reason for absence e.g. whether it was related to an infection.
- **Staff roles and numbers** (FTE, permanent and agency); funding (private/public) (collected at baseline and at the end of March). Care homes will also be asked to record any changes in staffing levels and funding since baseline.

### 6.8.2 Care home follow up data collection in INTERVENTION care homes

- **Air filters satisfaction questionnaire** (frequency: end of March): see section 6.10

## 6.9 Air filter data collection

All air filters will be assigned a unique identifier. Locations of each device will be recorded and a record of whether the device is being used in an individual bedroom, staff only area or communal area will be recorded.

If a consented resident in the intervention group moves room, their assigned air filter will be relocated to their new room. See also section 6.15.2.

### **6.9.1 Data collection in ALL care homes**

- **Use of additional air filters in communal, staff and private bedrooms** Care home managers will record if they have any new air filters (acquired outside of the study) in the care home since baseline and if so, the number of communal, staff or private resident bedrooms with air filters and whether they have been switched on (see section 5 for eligibility criteria).

### **6.9.2 Data collection in INTERVENTION care homes**

- **Fidelity data:** Intervention study champions/ managers will record the following data relating to the use of all (both private and communal room) air filters
  - Fidelity measures: checklist regarding location as planned (including whether residents with air filter in private bedrooms have the filters assigned to them (frequency: weekly), switched on (frequency: daily), electricity use (frequency: weekly).
  - Filter maintenance (frequency: weekly) air filter unit is cleaned, filter replacement requirement checked.

### **6.9.3 Data collection in CONTROL care homes**

- **Installation and use of new air filters in private rooms for consented residents only (frequency: daily) (see 6.7.4)**

## **6.10 Staff questionnaires**

Staff will complete the questionnaire via an online survey or on paper. Staff will be provided with freepost envelopes to send their completed questionnaire to the central study team for entry onto the database. Staff that are involved in consenting residents will not be asked to complete the questionnaires.

